## PROJECT SUMMARY

**Study Title:** Time for Lunch: The Impact of Seated Lunch Time Constraints on Child Eating Behaviors

**Sponsor:** United States Department of Agriculture Hatch Project #ILLU-698-315.

**Background and Significance:** Recent peer-reviewed observational evidence suggests that school children receive anywhere from 10-33 minutes of seated lunch time and that students with less time to eat discard higher amounts of milk, entree (i.e. protein items), grains, and vegetables. This waste is a missed opportunity for improved nutritional security and healthy habit development. The purpose of this study is to estimate the impact that lunch time constraints have on child food selection, consumption and waste behaviors using a crossover trial design, where seated lunch time is randomly allocated to be either 10 minutes or 20 minutes each day.

## STUDY DESIGN

**Study Type:** Crossover clinical trial (interventional)

**Allocation:** Randomized

**Masking:** None (Open Label)

**Study Timeframe:** June 3, 2019 – June 28, 2019

This study takes place over four consecutive weeks for five days (Monday through Friday) for a total of 20 study days.

**Intervention/Treatment:** The primary intervention of interest is the time constraints during school meals, randomly assigning either 10 minutes or 20 minutes of seated lunch time to each study day.

### Eligibility Criteria:

- Elementary and middle school-aged children attending a university summer camp
- Parent written consent to participate
- Children provide own assent to participate
- Children eat provided camp lunch

**Treatment Plan & Randomization:** Participants are served school lunches that met National School Lunch Program (NSLP) nutrition standards. Over the course of 20 study days, there are 10 days assigned to each lunch period: a) 10 minutes of seated lunch time and b) 20 minutes of seated lunch time. Five menus were served throughout the course of the study in order to provide variation to the lunches. Lunch time was randomly assigned within each menu so there is a total of two repetitions of each menu and lunch time.

Table 1. *Lunch time assignment and menu pairings\* by Study Day*

| Week: | Monday                     | Tuesday                    | Wednesday                  | Thursday                   | Friday                     |
|-------|----------------------------|----------------------------|----------------------------|----------------------------|----------------------------|
| 1     | June 3
A
10 minutes  | June 4
B
20 minutes  | June 5
C
10 minutes  | June 6
B
10 minutes  | June 7
D
20 minutes  |
| 2     | June 10
A
20 minutes | June 11
E
10 minutes | June 12
C
20 minutes | June 13
E
20 minutes | June 14
D
10 minutes |
| 3     | June 17
A
10 minutes | June 18
B
10 minutes | June 19
C
10 minutes | June 20
B
20 minutes | June 21
D
20 minutes |
| 4     | June 24
A
20 minutes | June 25
E
10 minutes | June 26
C
20 minutes | June 27
E
20 minutes | June 28
D
10 minutes |

\*There are 5 different menus (labeled A-E). Each menu was served 4 times over the course of the study, consisting of two menu-lunch time dyads occurring during the study period. The lunch time was randomly determined for the first and third occurring menu date, and the alternate lunch time was assigned to the second and fourth occurring date accordingly.

**Treatment Arms:** Due to logistics, there will be only one sequence of menu and length of lunch throughout the study.

## STUDY RECRUITMENT AND STUDY POPULATION

**Recruitment:** Study participants will be recruited from a university summer camp. All children who sign up for a university summer camp will be invited to participate in the study. Lunch will be provided for free to all children as a benefit, regardless of study participation. There were no additional incentives to participate in the study.

Parents will be sent information about the study, a consent form, and demographic form electronically when signing up for the summer camp. Parents can complete the consent form electronically or bring a hard copy the first day of camp. Parents will also fill out a demographic information form for their child along with the consent form. During the first day of camp, children will provide written assent to participate on the first day of camp each week.

Children can sign up for 1-4 weeks of camp and therefore were not expected to participate in every study day.

## METHODS

### Menu Plans:

The five menus to serve throughout the study (serving size and NSLP meal component):

Menu A:

- Grilled chicken sandwich on a whole grain bun (2 oz meat, 1-2 oz grain) **OR**
- Whole grain pasta w/ marinara sauce (2 oz grain) and meatballs (2 oz meat)

*Study Protocol for:*

Time for Lunch: The Impact of Lunch Time Constraints on Child Eating Behaviors

- Corn (½ C starchy vegetable)
- Broccoli (½ C dark green)
- Grapes (½ C fruit)
- Peaches (½ C fruit)

Menu B:

- Cheese, sausage, or pepperoni pizza (2 oz meat alternative, 2 oz grain) **OR**
- All beef hot dog (2 oz meat/1-2 oz grain)
- Baby carrots (½ C red/orange vegetable)
- Zucchini coins (½ C other vegetable)
- Pineapple (½ C fruit)
- Fresh apple slices (½ C fruit)

Menu C:

- Hamburger/Cheeseburger on whole grain bun (2 oz meat/2 oz grain) **OR**
- Crunchy beef tacos (2 oz meat) with Spanish rice (1 oz grain)
- French fries (½ C starchy vegetable)
- Refried beans (½ C beans/legumes vegetable)
- Pears (½ C fruit)
- Honeydew (½ C fruit)

Menu D:

- Beef with broccoli (2 oz meat and ½ C vegetable) and brown rice (2 oz grain) **OR**
- Sliced turkey and cheese on whole grain sub (2 oz meat/2 oz grain)
- Steamed broccoli (½ C dark green vegetable)
- Steamed cauliflower (½ C other vegetable)
- Mandarin oranges (½ C fruit)
- Peaches (½ C fruit)

Menu E:

- BBQ beef sandwich (2 oz meat) **OR**
- Orange chicken (2 oz meat) and brown rice (2 oz grain)
- Potato wedges (½ C starchy vegetable)
- Sliced red peppers (½ C red/orange vegetable) with pre-portioned ranch
- Strawberries (½ C fruit)
- Apple slices (½ C fruit)

*\*1% unflavored milk or nonfat chocolate milk served with each meal*

Menus will conform to the National School Lunch Program nutrition standards. Food will be prepared by a University chef with assistance from graduate and undergraduate student researchers in a commercial kitchen. All persons involved in preparing meals had a certificate of food handler training. Temperature monitoring and other food safety procedures were strictly followed during food preparation and service.

Menus are designed using MOSIAC software and featured the same foods served to the local school district using the same distributor when possible.

**Training of Research Staff:**

Research assistants participate in several trainings prior to the start of the study. The first training taught researchers how to complete their respective roles for data collection (e.g., observational data, food waste measurement) and allowed them to practice with each other. The second training consisted of a complete rehearsal of an entire study, including meal production and reference weight collection, participant observation of seated lunch time and social behaviors, and measuring wasted food. During the second training, table layout and placement was refined so that observers could have an unobstructed view of all participants. All research staff also complete CITI ethics trainings and, for research assistants involved in food preparation, food handler training.

**Lunchroom Setup and Layout:**

Tables are spaced around the lunchroom so that observers are at their own tables with clear sight lines to participants. (Lunchroom layout shown below). Additional observers may stand along the walls (wherever allows clear sightlines) of the room to provide extra observations of participants so that observers reliability can be assessed. Seated observers are provided smaller portions of the same food served to participants to make their observations less noticeable to the participants.

Once participants exit the lunch line, they are permitted to sit at whichever open seat they choose but are not allowed to move chairs.

[figure not shown]

### Food Preparation:

For weighing pre-consumption standardized reference weight, five extra servings of each food item will be made, portioned out via standard sized serving utensils, and weighed to the nearest 0.5 grams. The weights of these five samples will be averaged. This average weight will be used as the reference weight.

Foods that are individually packaged (e.g., chicken sandwiches) and have larger weight variation range will be weighed and labeled individually in lieu of reference weights. These items will be marked with a sticker (labeled A-Z) that will be used to track the item's specific weight. A sticker weight log will be used to keep track of stickers and their corresponding weights so that this information will not be visible to participants.

For all foods, inedible portions (cores, peels, etc.) are extracted before the reference weight is measured.

Participants were also offered a healthy snack prepared by research staff at the same time each morning and did not participate in any physical activity before lunch each day. Lunch took place inside the Spice Box, which is a dining space within the department of Food Science and Human Nutrition at the XXXX. At 12:30 pm each day of camp, participants would enter the Spice Box for lunch and immediately be informed if there would 10 or 20 minutes of seated lunch time. Participants were then directed to enter the lunch line, which was located in the adjacent commercial kitchen, very close to the Spice Box entrance.

*Study Protocol for:*

*Time for Lunch: The Impact of Lunch Time Constraints on Child Eating Behaviors*

**Lunch Period:**

At the start of lunch, participants will form a line to enter the food serving area. Once participants are lined up, a research staff member will make an announcement about the length of seated lunch time for that day. Participants will retrieve their participant ID card and then move through the lunch line.

All food items will be pre-portioned, meaning there will be no option to select portion sizes of items. Children will be instructed to select menu items that qualify as a reimbursable lunch as defined by the National School Lunch Program. Thus, participants are required to select three different components and one must be a fruit or vegetable. (All entree items constituted two meal components: grain and protein). A researcher will check each participant's tray to ensure they have a reimbursable meal after exiting the serving line.

While selecting food items in the lunch line, participants will verbally ask for the food items they want, and research staff will serve the pre-portioned meal items (offer vs. serve format of the National School Lunch Program). Foods will be pre-portioned on small plates, food boats, or bowls. Food components that are hot will be served first due to the arrangement of the buffet equipment.

As participants exit the lunch line, a pre-consumption photo is taken of their selected food items. An ID card with the participant ID number will be included in each tray photograph.

Seated lunch time will officially begin when the last participant makes it through the line and sits down. At this time, a researcher will announce the exact time that lunch ends and will write the time on a poster. The researcher will make an additional announcement when five minutes remain for lunch.

Participants will not be allowed to get seconds on food items, however participants are allowed refills of water. Participants can also get up for condiments and utensils during lunch.

At the end of lunch, a final announcement is made for participants to walk their trays to the corner of the room to collect tray items for weighing.

**Data Collection During Lunch Period:**

1. Meal component selection: a research staff member takes a photograph of each child's lunch to document selection (which meal component were chosen).
2. Line order: the number order of each child as they leave the survey line, as recorded by a research staff member and documented with a time stamp on the pre-consumption photos.
3. Seat layout: a research staff member documents where each participant sits at the study tables
4. Water refills: a research staff member documents all cups of water children get (unlimited refills were available), recording both the number of cups and the participant ID number.
5. Participant observations: at least one research staff member will observe each participant during lunch time to record information about: time a participant sits down, time a participant stands up, any additional time a participant is not seated in their chair, phone rating and talking during lunch, notes on any food that is spilled or traded, and other notes that may be helpful

during data analysis. *Note: some participants will have multiple observers to provide estimates of inter-rater reliability.*

6. Cover sheet: student researchers will fill out a cover sheet for each study day that includes information about weather and what time lunch started and ended each day.

#### **Data Collected Immediately Following the Lunch Period:**

1. Food preference surveys: after handing in their trays, participants will fill out a post-meal survey indicating their preferences on how the food looked and tasted.
2. Food Waste Measurement: A post-consumption photo of each tray will be taken at the end of lunch prior to weighing food items. Each food component (entree, fruit, vegetable) remaining on the tray as food waste will be weighed separately to the nearest 0.5 gram after the lunch period and recorded on weight sheets. Inedible portions of food items will not be weighed (e.g. food bowls, napkins). Beverage waste remaining on the trays will be recorded to the nearest 0.5 mL using a graduated cylinder.

## **STATISTICAL ANALYSIS**

### **Measures:**

#### *Sample Size:*

The sample size for this study was fixed based on the summer camp enrollment. A sample size or power calculation was not conducted due to this restraint.

#### *Seated Lunch Time:*

Seated lunch time will be measured in two ways in this study. The first measure will be a categorical variable that indicates the randomly assigned seated lunch time: 10 minutes or 20 minutes. There will be a total of 10 10-minute days and 10 20-minute days throughout the study.

The second measure will use the actual time a participant is seated eating lunch. This continuous variable will be calculated using the actual observed seated lunch time. The total seated lunch time is calculated as the time a participant stood up at the end of lunch minus the time a participant sat down at the beginning of lunch. Additional non-seated time recorded on the observer sheet will be subtracted from this lunch time to account for time a participant may have gotten up after initially sitting down.

Inter-rater reliability was assessed for 27.4% of trays during the study that had multiple observers for the same participant. The inter-rater reliability for both the length of lunch and non-seated time had excellent agreement as measured by the intra-class correlation coefficient

- Observed length of lunch: 0.998 (95% CI: 0.997, 0.999)
- Non-seated time: 0.954 (95% CI: 0.888, 0.979)

#### *Food Consumption and Food Waste:*

The primary outcomes of interest will be the percent of food items selected, percent of food consumed, and the amount of food wasted. Each outcome will be broken down by meal component: entree, fruit, vegetable, beverage (milk and water), and milk alone.

- Selection: percent of students selecting each meal component
- Percent consumed:  $\frac{\text{Reference value} - \text{amount left on tray}}{\text{Reference value}} * 100$  (where the reference value is the pre-consumption weight)
- Amount wasted: amount of meal component remaining on the tray at the end of lunch, reported in grams (entrée, fruit, and vegetable) or milliliters (beverages)

#### *Nutrient Analysis:*

The nutritional profile of all foods served will be determined using the Nutrition Data System for Research. For each food item, nutrients consumed and nutrients wasted will be calculated as follows:

- Nutrients consumed: Percent consumed\*reference nutrient (where the reference nutrient is the pre-consumption value)
- Nutrients wasted: Percent wasted\*reference nutrient (where the reference nutrient is the pre-consumption value)

Nutrients will be calculated for individual meal components as well as the total meal. The total meal nutrients will be a sum of the nutrients consumed/wasted from each meal component.

#### *Observed Social Behaviors:*

Talking and phone use ratings from the observer sheets will range from a scale of zero to five during the first part of lunch and the last five minutes. An overall rating during lunch will be calculated as the average of the rating for the first part of lunch and the last five minutes.

Inter-rater reliability was assessed for 32.8% of trays during the study that had multiple observers for the same student. The inter-rater reliability for both talking and phone use had excellent agreement as measured by the intra-class correlation coefficient:

- Talking: 0.954 (95% CI: 0.932, 0.967)
- Phone use: 0.967 (95% CI: 0.954, 0.976)

#### **Analysis Plan:**

*Descriptive statistics:* Descriptive statistics will include a count of participants and total trays, frequencies of categorical demographic information, and mean and standard deviation of continuous demographic information.

*Selection:* Percent of participants who select each food item overall and broken down by 10-minute and 20-minute seated lunch time. Chi square tests can compare the differences in selection distribution between 10-minute and 20-minute seated lunch time .

*Model parameters:* Mixed effects linear regression models will assess all continuous outcome measures and will include the following:

- Random effects: participants (to control for repeated measures)
- Fixed effects: menu (5 levels), prior menu exposure (4 levels), average talking rating, average phone use rating.

- For amount wasted and all nutrient models: an additional fixed effect of the reference weight/volume or reference nutrient (to control for variability of available food/nutrients pre-consumption)

For models that include the categorical time (10-minute and 20-minute seated lunch time), the estimated marginal means (emmeans) will be used to compare the mean outcome for 10-minute and 20-minute seated lunch time. The contrast between the means (10 minute-mean minus 20-minute mean) will also be reported along with a p-value. Models that used continuous time variable will assess the beta coefficient, t-value, and p-value. Beta coefficients will represent the change in outcome for a one minute increase in seated lunch time.

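### Selection is compared as raw 10- versus 20-minute percentages without menu, so a primary outcome is open to menu-mix bias if attendance in weeks 1 and 3 differs from weeks 2 and 4

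*Protocol*

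**What the plan says.** The protocol's section on Food Consumption and Food Waste makes selection a primary outcome: "The primary outcomes of interest will be the percent of food items selected, percent of food consumed, and the amount of food wasted". It is reported by meal component and defined as follows: "Selection: percent of students selecting each meal component".

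The Analysis Plan summarises it as "Percent of participants who select each food item overall and broken down by 10-minute and 20-minute seated lunch time" and tests it thus: "Chi square tests can compare the differences in selection distribution between 10-minute and 20-minute seated lunch time". Menu appears in neither statement. The models that follow are for other outcomes: "Mixed effects linear regression models will assess all continuous outcome measures and will include the following". Those do carry menu: "Fixed effects: menu (5 levels), prior menu exposure (4 levels), average talking rating, average phone use rating".

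On design, the Treatment Plan & Randomization text says: "Lunch time was randomly assigned within each menu so there is a total of two repetitions of each menu and lunch time". Every child follows the same calendar (Treatment Arms). On attendance, the Recruitment text says: "Children can sign up for 1-4 weeks of camp and therefore were not expected to participate in every study day".

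**The concern.** The design balances menu and lunch time by counting days, whereas selection is counted over children's trays. The number of trays on a day depends on who signed up that week. For menus A, C and D the two lunch times fall in different weeks, so uneven attendance can give the pooled 10-minute trays a different menu mix from the pooled 20-minute trays. The vegetables on offer differ by menu (for instance fries and refried beans on C, carrots and zucchini on B). A difference in mix could therefore look like an effect of lunch length, or mask one.

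This concerns the point estimate. It is separate from the dependence between repeated trays of one child: correcting the standard error for clustering would leave the menu-mix bias in place.

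**Working it through.** **Inputs.** Menu, lunch time and week of all 20 days come from Table 1 of the protocol. The protocol gives no weekly attendance and no selection rates, so both are assumptions below. Trays are taken as the unit, and attendance as constant within a week.

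**1. The plan's own balance.** Counting Table 1 gives 10 ten-minute and 10 twenty-minute days, with two days in each of the 10 menu-by-time cells. The stated balance is correct for days.

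**2. Where each cell falls.**

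| Menu | 10-minute weeks | 20-minute weeks |
|---|---|---|
| A, C | 1, 3 | 2, 4 |
| D | 2, 4 | 1, 3 |
| B | 1, 3 | 1, 3 |
| E | 2, 4 | 2, 4 |

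**3. Menu mix.** Let r be total attendance in weeks 1 and 3 divided by total attendance in weeks 2 and 4. The trays for A:B:C:D:E are in the ratio

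- 10 minutes: r : r : r : 1 : 1, sum 3r + 2
- 20 minutes: 1 : r : 1 : r : 1, sum 2r + 3

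At r = 1 each menu is 20% of trays at both lunch times. At r = 1.5, A and C together are 3/6.5 = 46.2% of 10-minute trays and 2/6 = 33.3% of 20-minute trays; D is 1/6.5 = 15.4% and 1.5/6 = 25.0%.

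**4. Raw difference when lunch length has no effect.** This is the sum over menus of (share at 10 minutes − share at 20 minutes) × selection rate. Assume a rate of 60% on B and E, 60 + d on A and C, and 60 − d on D. The difference becomes

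d × [(2r − 1)/(3r + 2) − (2 − r)/(2r + 3)].

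| r | Bracket | d = 20 points | d = 10 points | d = 5 points |
|---|---|---|---|---|
| 0.5 | −0.375 | −7.5 | −3.8 | −1.9 |
| 1 | 0 | 0 | 0 | 0 |
| 1.25 | 0.125 | 2.5 | 1.2 | 0.6 |
| 1.5 | 0.224 | 4.5 | 2.2 | 1.1 |
| 2 | 0.375 | 7.5 | 3.8 | 1.9 |

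For example, at r = 1.5 and d = 20:

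- 10 minutes: 0.8 × 0.462 + 0.6 × 0.385 + 0.4 × 0.154 = 66.2%
- 20 minutes: 0.8 × 0.333 + 0.6 × 0.417 + 0.4 × 0.250 = 61.7%

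**5. Effect on the test.** This was simulated with no lunch-time effect, independent trays, a two-sided 5% level and 20,000 runs. At d = 20 the pooled chi-square rejected in 9.5% of runs with 15 children in weeks 1 and 3 against 10 in weeks 2 and 4, and in 26.5% with 20 against 10. At d = 5 the figures were 5.0% and 6.5%. A Cochran-Mantel-Haenszel test stratified by menu stayed between 4.9% and 5.1% throughout.

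**6. When the bias is small or absent.**

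- Only the two totals matter. Weekly attendance of 10, 20, 20, 10 gives 30 against 30, so r = 1 and no bias.
- A steady decline partly cancels: 20, 18, 16, 14 gives 36/32 = 1.125, and 24, 20, 16, 12 gives 40/32 = 1.25.
- The pattern of rates matters. With A at 40%, C at 80% and the rest at 60%, the bias is 0 at every r, because A and C always have equal shares. If only C differs (80% against 60%), it is 20 × (0.231 − 0.167) = 1.3 points at r = 1.5.

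**The case against.** The strongest reply is that nothing in the protocol shows the imbalance occurred. Because the weeks alternate, a ratio of 1.5 or 2 needs a marked alternating pattern of attendance that the text does not suggest. The assumed rates are also aligned so that the bias adds up: A is grouped with C at the high end, although A, like D, serves broccoli. Both points stand. They limit the size and make the bias conditional.

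Scope is narrower than all components. The same two milks come with every meal, so the milk and beverage offer does not vary by menu. Every menu offers two entrees, and an entree supplies two of the three components required, so entree selection is plausibly high throughout, though no rate is given. That leaves mainly fruit and vegetables. For a single item, menu mix enters only if trays from days when the item was not offered are in the denominator, and the plan does not say whether they are.

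Finally, the chi-square wording is permissive, the SAP is not at hand, and a model for repeated trays might settle both matters. The last is true only if that model includes menu. The protocol does state an analysis for selection, the only one it gives, and it omits the stratum within which lunch time was randomised. That is more than detail left for later.

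**Conclusion.** The point holds as a conditional one. A primary outcome is left open to a menu-mix bias that the same plan adjusts for in its continuous models. Bias arises only if attendance in weeks 1 and 3 together differs from that in weeks 2 and 4 together, and if component selection differs between menus in a way that does not cancel. With d between 10 and 20 points it is about 1 to 2.5 percentage points at a ratio of 1.25 and about 4 to 7.5 at 2, and smaller with a narrower spread. The direction depends on which weeks are fuller and which menus are better liked.

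A reader might infer that any unequal weekly attendance confounds lunch time with menu, or that the selection results are in fact biased. The documents support neither: unequal weeks can give equal totals, and no counts or rates are stated. Nor should one infer that stratifying by menu settles everything. It removes menu-mix bias, but for A, C and D it still compares partly different children across weeks. The change is worth making because it is cheap and can alter the estimate.

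**What to change.** In the Analysis Plan's selection paragraph:

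- Test the lunch-time effect on selection of each component in a logistic mixed model with menu as a fixed effect and participant as a random effect, as the continuous models have. Menu deals with the mix; the participant effect is needed because A, C and D compare partly different children.
- Report menu-standardised selection percentages for 10 and 20 minutes, with equal weight to the five menus.
- For single food items, use as denominator only trays from days on which the item was offered.

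Tray counts by week, set beside these results, would show whether the imbalance arose. The cost is a few sentences and a little more analysis of data already collected; menu and lunch time are known for every tray from Table 1.

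### Selection, a primary outcome, is compared by an unadjusted chi-square test although the 20-minute lunch is the second serving in 7 of 10 same-menu dyads, so part of any repeat-serving effect is credited to lunch length

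*Protocol*

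**What the plan says.** The protocol's section on food consumption and food waste makes selection primary: "The primary outcomes of interest will be the percent of food items selected, percent of food consumed, and the amount of food wasted". It defines selection as the percentage of students choosing each meal component.

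The Analysis Plan then splits the methods. For selection it gives percentages by lunch time and the statement "Chi square tests can compare the differences in selection distribution between 10-minute and 20-minute seated lunch time". The adjusted analysis is reserved for other outcomes: "Mixed effects linear regression models will assess all continuous outcome measures and will include the following". What follows is a participant random effect and "Fixed effects: menu (5 levels), prior menu exposure (4 levels), average talking rating, average phone use rating". Selection is yes or no on each tray, so this list does not reach it.

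On the design, the note to Table 1 says "Each menu was served 4 times over the course of the study, consisting of two menu-lunch time dyads occurring during the study period". Lunch time was drawn at random for the first and third serving of each menu, and "the alternate lunch time was assigned to the second and fourth occurring date accordingly". Under Treatment Arms the protocol adds that "there will be only one sequence of menu and length of lunch throughout the study".

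**The concern.** With one sequence for everybody, no second group of children meets the menus in the opposite order. If one lunch time falls more often on the later serving of a menu, serving order and lunch length are partly mixed up in a raw comparison. Enrolling more children on the same sequence does not remove this.

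The sponsor treats prior exposure as relevant, since it enters every model for a continuous outcome. The protocol gives no reason why familiarity with a menu should affect how much children eat but not what they ask for. Children hear the day's lunch time before they choose, so the selection comparison is a real test of lunch length and needs the same protection. What is at stake is a primary comparison that could be shifted by serving order while consumption and waste are protected from it.

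**Working it through.** **Inputs.** The 20 days of Table 1; dyads are servings 1 and 2, and servings 3 and 4, of each menu. Attendance of 1 to 4 weeks comes from the Recruitment section. The repeat-serving effect d (percentage points) is not in the protocol and is assumed.

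**1. The plan's own balance, reproduced.** There are 10 ten-minute and 10 twenty-minute days, and each menu appears twice at each lunch time. This agrees with the protocol.

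**2. Order within menu, read from Table 1.**

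| Menu | Servings 1, 2, 3, 4 (minutes) | Dyads with 20 minutes second | Mean prior servings, 20 minus 10 |
|---|---|---|---|
| A | 10, 20, 10, 20 | 2 | 2.0 − 1.0 = +1 |
| B | 20, 10, 10, 20 | 1 | 1.5 − 1.5 = 0 |
| C | 10, 20, 10, 20 | 2 | +1 |
| D | 20, 10, 20, 10 | 0 | 1.0 − 2.0 = −1 |
| E | 10, 20, 10, 20 | 2 | +1 |

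The 20-minute lunch is second in 2 + 1 + 2 + 0 + 2 = 7 of 10 dyads.

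**3. Prior servings, child attending all four weeks.** By serving number, the 10-minute days number 3, 2, 4, 1 and the 20-minute days 2, 3, 1, 4.

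- 10 minutes: (3×0 + 2×1 + 4×2 + 1×3)/10 = 1.3
- 20 minutes: (2×0 + 3×1 + 1×2 + 4×3)/10 = 1.7
- Difference: 0.4

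Stratifying by menu does not help: the last column of the table averages (1 + 0 + 1 − 1 + 1)/5 = 0.4.

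**4. Other attendance.** A child attending one week repeats only menu B (weeks 1 and 3) or menu E (weeks 2 and 4). With equal numbers in each single week, 3 of 10 twenty-minute days and 1 of 10 ten-minute days are repeats, so mean prior servings are 0.3 v 0.1. Over all 15 possible combinations of weeks, the 20-minus-10 difference in a child's mean prior servings is positive in 14 (0.14 to 0.60). It is negative only for week 1 alone (0 − 0.33 = −0.33).

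**5. Carry-over into the raw 20-minus-10 difference, with no true lunch-time effect, at full attendance.**

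- Shift of d per prior serving: (1.7 − 1.3)d = 0.4d
- Shift of d at the second serving of a dyad: (7/10 − 3/10)d = 0.4d
- First serving differs by d from all later ones: later servings are 8/10 of 20-minute and 7/10 of 10-minute days, so 0.1d

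| Assumed d | 0.4d | 0.1d |
|---|---|---|
| 2 points | 0.8 | 0.2 |
| 5 points | 2.0 | 0.5 |
| 10 points | 4.0 | 1.0 |

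For equal single weeks the figure is (0.3 − 0.1)d = 0.2d.

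**The case against.** **The imbalance arose by chance.** The first serving of each dyad was randomised, and a split of 7 to 3 or worse in either direction has probability 2 × 176/1024 = 0.34. A reader might infer that the randomisation failed; nothing in the protocol supports that. But the realised sequence is fixed, known and common to all children, so the case for adjusting stands.

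**The whole repeat effect does not transfer.** A reader might infer that a repeat-serving effect would simply be reported as a lunch-time effect. The recount does not bear this out: at full attendance between a tenth and four tenths of d carries over, depending on the shape. For children attending week 1 only, the imbalance reverses. If only the first serving differs from later ones, it also reverses for children attending weeks 1 and 3 (2/4 − 4/6 = −0.17). The net direction depends on an attendance mix that the protocol does not give.

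**d may be small.** On the per-serving reading, the 4-point figure needs d = 10, which means a 30-point change from first to fourth serving; nothing in the protocol supports a change of that size. Selection is defined by component, and each menu offers two entrees, two fruits and two vegetables, so swapping one entree for the other on a repeat day leaves the outcome unchanged. Milk is the same with every menu. This stands as a limit on the size.

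**An error rate cannot be attached.** A reader might want to infer an inflated false-positive rate. That would need tray counts, selection rates and the correlation between a child's trays, none of which is given. Because children can contribute trays at both lunch times, treating trays as independent can also make the chi-square test conservative.

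**The wording is permissive, and a separate SAP may say more.** The protocol says only that the test can be used. Yet it states no other comparison for selection, while it sets out an adjusted model for the other outcomes.

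**Conclusion.** The point holds as a partial confounding of one primary comparison. Selection is primary, its only stated test is unadjusted, and in the single sequence the 20-minute lunch is the second serving in 7 of 10 dyads. Part of any repeat-serving effect on selection is therefore credited to lunch length: about 0.4d or 0.1d at full attendance, according to the shape of the effect, and 0.2d per prior serving if equal numbers attend single weeks. These figures rest on Table 1 and on assumed values of d and attendance. The actual bias is unknown and could be negligible. The documents do not support saying that the selection result will be wrong, or in which direction. This is a cheap improvement that brings selection into line with the other primary outcomes.

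**What to change.** In the Analysis Plan, replace the chi-square test as the selection comparison with a mixed-effects logistic model, or GEE, for selection of each meal component. Fixed effects: lunch time, menu (5 levels) and prior menu exposure (4 levels). Participant enters as a random effect, or as the cluster in GEE, which also handles repeated trays from the same child. Report the adjusted 10- v 20-minute difference and keep the raw percentages by lunch time as description.

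The cost is a little more analysis work, with a covariate that the plan already uses, and a modestly wider standard error for the lunch-time contrast. In a linear model with a participant effect, adding the exposure factor widened it by about 5 to 12% over the attendance patterns assumed (for example 0.1118 against 0.1000, a ratio of 1.12, and 0.1019 against 0.0970, a ratio of 1.05). The logistic figure may differ somewhat. The plan already includes this factor in the models for its other primary outcomes.
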